## Abstract

**Background:**

Depression and anxiety are common co-morbid health problems in patients with type 2 diabetes. Both depression and anxiety are associated with poor glycaemic control and increased risk of poor vascular outcomes and higher mortality rates. Results of previous studies have shown that in clinical practice, treatment of depression and anxiety is far from optimal as these symptoms are frequently overlooked and undertreated.

**Methods/Design:**

This randomised controlled trial will examine the effectiveness of a disease management programme treating symptoms of depression and anxiety in primary care patients with Type 2 diabetes. Patients will be randomized on patient level in 1:1 ratio. Random block sizes of 2 and 4 are used. The disease management programme consists of screening, stepped treatment and monitoring of symptoms (n = 80). This will be compared to care as usual (n = 80).

**Discussion:**

The disease management model for co-morbid depression and anxiety in primary care patients with diabetes is expected to result in reduced symptoms of depression and anxiety, improved quality of life, reduced diabetes specific distress and improved glyceamic control, compared to care as usual.

**Trial Registration:**

Dutch Trial Register NTR2626

## Background

Diabetes mellitus is a common chronic disease affecting more than 220 million patients worldwide, with approximately 90% having type 2 diabetes (DM2) [1]. Patients with DM2 often have co-morbid affective symptoms such as depression and anxiety. Results of recent studies show that 10-30% of patients with DM2 suffer from major depressive disorder or sub-threshold depression [2-4], about 14% suffers from generalized anxiety disorder and up to 40% has an elevated level of anxiety symptoms [5]. A meta-analysis of longitudinal studies showed that diabetes patients are also at a 24% increased risk of developing depression [6].

The high prevalence of depression and anxiety in patients with DM2 has significant negative implications. It is associated with poorer quality of life, impaired self-care activities, higher health care costs, a higher risk for the development of diabetes complications, and increased mortality rates [7-13]. Despite these known adverse effects and the high prevalence of depression and anxiety in DM2, and the fact that effective treatments are available, there is a considerable underdetection and subsequent undertreatment of these conditions [14,15]. Less than half of the depressed and/or anxious patients with diabetes are recognised as such [14,15]. In order to prevent the negative consequences of anxiety and depression, early detection and enhanced treatment thus seem crucial.

Meta-analyses have shown that treating depression and anxiety in patients with DM2 results in reduced psychological distress, but also in improved glyceamic control [16,17]. For example, the meta-analyses by Ismail et al. showed that psychological interventions resulted in a significant better glyceamic haemoglobin, with an absolute difference of 0.76% (or 76 mmol/mol) [16]. A study by Bogner et al. has shown that the all cause mortality risk decreased when treating depression in primary care patients with diabetes mellitus [7]. However, the study by Bogner has been criticized by Thombs and Ziegelstein [18]. Given the high prevalence of depression and anxiety in patients with DM2, and the fact that these emotional problems are often overlooked and undertreated, while effective treatments are available, current guidelines recommend screening for depression and anxiety [19-21]. A recent randomised controlled trial showed, however, that screening alone did not improve depression outcomes in secondary diabetes care [22]. It seems crucial that screening efforts should be embedded in a managed care approach for depression/anxiety [23].

A large American randomised controlled trial, The Pathways Study, tested the effectiveness of a collaborative care approach consisting of screening, stepped care intervention and collaboration between several health professionals (multidisciplinary team) [24]. The collaborative care approach was more effective in reducing depressive symptoms compared to usual care (z = 2.84, P = 0.004 after 6 months). It was also cost-effective [25]. However, no effect on glyceamic control was found [24]. Another randomised controlled trial (n = 361) has been conducted in the Netherlands in elderly primary care patients with diabetes or COPD and co-morbid depression [26]. The intervention, provided at home by trained nurses, was based on CBT principles and self-management. While the intervention was effective in reducing depressive symptoms (BDI improvement rate OR = 3.22 [1.31 - 7.89]), it was not cost-effective [27].

Most research focused on treating depression, and less research has investigated a treatment for anxiety in patients with DM2. The randomised controlled trials investigating anxiety treatment in patients with diabetes show less consistent results compared to the depression trials; some studies showed a beneficial effect while other did not [5,28].

In the present study, we therefore aim to test the effectiveness of a disease management intervention. It will be tested whether and to what extend the **Di**sease **Ma**nagement intervention for **Co**-morbid **De**pression and **A**nxiety in patients with **DM2**(DiMaCoDeA-DM2) can significantly reduce symptoms of depression and anxiety. Using a randomised controlled trial design, we will compare the new intervention to care as usual. Our primary objective is to investigate the effectiveness of the disease management approach on symptoms of depression and/or anxiety. Our secondary objectives are to investigate whether this approach results in improved quality of life, reduced diabetes-specific emotional distress, improved lifestyle and self care behaviours, and lower health care costs.

## Methods/Design

### Eligibility criteria

Eligible patients are type 2 diabetes mellitus patients, aged 18 or over and with elevated depressive (PHQ-9 score ≥ 7) and/or anxiety symptoms (GAD-7 score ≥ 8; see 'assessment' for more information about the PHQ-9 and GAD-7). Patients will be excluded if they currently receive psychological treatment for their symptoms of depression or anxiety, experience major psychiatric problems, such as schizophrenia and suicidal ideation, are addicted to alcohol, drugs or gambling, are cognitively impaired, or are unable to read or speak Dutch sufficiently.

### Study setting and sample recruitment

The study will be conducted in primary care practices that are affiliated to a large primary care organisation PoZoB (Praktijkondersteuning Zuidoost Brabant). Over 200 general practitioners and approximately 150 practise nurses in a southern region of the Netherlands are associated with PoZoB with approximately 12.000 patients with DM2. The general practitioners, together with the practice nurse are responsible for the primary care of patients with chronic diseases such as DM2. Patients with DM2 are seen by the practice nurse every three months.

Patients with DM2 from the general practices that agreed to participate will be screened for symptoms of depression or anxiety with the PHQ-9 and GAD-7. Eligible patients will be invited for an interview. During this interview the baseline questionnaires will be administered. When eligible patients agree to participate and after they have given written informed consent, they will be randomised into the intervention group or the care as usual group.

### Randomisation

Patients will be randomised on patient level in equal ratio (1:1). Block randomisation will be used with block sizes of 2 and 4. These block sizes are chosen to enhance the chance that in each general practice patients will be in both study conditions. An independent researcher will generate a random sequence by http://randomization.com and will fill envelopes with the sheets describing the group allocation. These opaque envelopes will be sealed and sequentially numbered by the independent researcher. When a participant is enrolled in the study, the person who enrols the participant will open the envelope and disclose the group allocation. The allocation sequence will be concealed until a participant is irreversibly registered.

### Power

Assuming an α of 0.05 and a 1-β (power) of 0.90, 64 participants are needed in each condition to be able to detect a moderate effect of 0.5 standard deviation on the PHQ-9 and GAD-7. We anticipate a drop out of 20% and therefore we will need to include 80 patients in both groups.

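### The stated 90% power is wrong: 64 evaluable patients per arm give 80% power for 0.5 SD (two-sided 0.05), and 80 per arm without drop-out give 88%

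*Protocol article*

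**What the plan says.** The sample size is justified in one place, the Power section under Methods/Design: "Assuming an α of 0.05 and a 1-β (power) of 0.90, 64 participants are needed in each condition", the aim being "to be able to detect a moderate effect of 0.5 standard deviation on the PHQ-9 and GAD-7". The next sentence adds the allowance for attrition: "We anticipate a drop out of 20% and therefore we will need to include 80 patients in both groups".

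The section does not say whether alpha is one- or two-sided, and it mentions no covariate adjustment or variance reduction. The Randomisation section gives equal allocation. The Statistical analyses section plans ANCOVAs and names age and sex as the adjustment variables.

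**The concern.** Every input to a standard two-sample calculation is printed: alpha, power, standardised effect, number per arm and allocation ratio. The number per arm does not follow from the others. For 0.5 SD at two-sided 0.05, 64 per arm is the familiar answer for 80% power, which suggests that the power was misstated or that a figure was taken from the wrong line of a table.

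What is at stake is the type II error the trial claims to control. The article implies a 10% chance of missing a moderate effect. If the true figure is about 20%, a non-significant result says less against such an effect than readers of the protocol would suppose. The error also carries into the enrolment target, because 80 per arm is derived from 64.

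**Working it through.** **Inputs (Power and Randomisation sections).** Alpha 0.05; power 0.90; standardised difference d = 0.5; 64 evaluable per arm; drop-out 20%; 1:1 allocation. Two-sided testing is assumed first, because sidedness is not stated; one-sided testing is tried below.

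**Step 1: reproduce the plan's figure.** The normal-approximation size per arm is

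n = 2 (z₁₋α/₂ + z₁₋β)² / d²

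- 90% power: 2 × (1.960 + 1.282)² / 0.25 = 84.1, so 85 per arm. The exact (noncentral t) solution is 85.03, so 86.
- 80% power: 2 × (1.960 + 0.842)² / 0.25 = 62.8, so 63 per arm. The exact solution is 63.77, so **64**.

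The printed 64 is reproduced exactly at 80% power and not at 90%.

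**Step 2: power at the planned sizes.** Power ≈ Φ(d√(n/2) − 1.960).

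| Per arm | Normal approximation | Noncentral t |
|---|---|---|
| 64 | Φ(2.828 − 1.960) = 0.807 | 0.801 |
| 80 (no drop-out) | Φ(3.162 − 1.960) = 0.885 | 0.882 |

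**Step 3: the drop-out step.** 64 / (1 − 0.20) = 80, which is correct. Starting from the size that gives 90%, it would be 86 / 0.80 = 107.5, so 108 per arm (107 from the normal-approximation 85).

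**Step 4: effect detectable with 90% power at 64 per arm.** (1.960 + 1.282) × √(2/64) = 0.573 SD by the normal approximation; 0.577 SD by noncentral t.

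**Step 5: can another reading give 64?**

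- *One-sided alpha 0.05.* n = 2 × (1.645 + 1.282)² / 0.25 = 68.5, so 69; noncentral t gives 69.2, so 70. Power at 64 is 0.879. This is closer but does not give 64.
- *Alpha split over the two primary outcomes (0.025 each).* This needs 100 per arm (normal) or 101 (noncentral t), and power at 64 falls to 0.712. The gap widens.
- *ANCOVA with a baseline covariate.* If the baseline score correlates r with the outcome, the residual SD shrinks by √(1 − r²), so the effective d is 0.5/√(1 − r²). The article gives no r, so a range is assumed:

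| Assumed r | Power at 64 per arm (noncentral t) |
|---|---|
| 0.3 | 0.837 |
| 0.4 | 0.865 |
| 0.5 | 0.900 |
| 0.6 | 0.939 |

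The correlation needed for 90% is 0.49 (normal) to 0.50 (noncentral t).

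**The case against.** The strongest reply is that the planned analysis is an ANCOVA, not a t-test. Baseline PHQ-9 and GAD-7 scores are collected, and if they enter the model with a correlation near 0.5 or above, 64 per arm do give about 90% power. The 20% type II error therefore applies to the unadjusted two-sided comparison and is not necessarily the error of the final analysis. That qualification stands. It does not rescue the sentence: the Power section invokes no variance reduction, the only covariates named are age and sex, and the exact match of 64 with the plain 80% figure makes a misstated power the likelier explanation.

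Sidedness is also unstated. Under one-sided 0.05 the shortfall at 64 per arm shrinks from about 10 points to about 2, and 80 per arm without drop-out would give 0.934. Yet the article claims 90% at 64, one-sided testing still needs 70, and nothing in the article points to a one-sided test.

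Two further points are fair. The 88% at 80 per arm only shows how far short the number is; the article does not claim 90% on the assumption of no drop-out. And 80% is a conventional power target, so the design remains usable. What is wrong is the power claimed for it. Nor can the mismatch be put down to condensation for a journal: the figure is printed with its assumptions and does not follow from them.

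**Conclusion.** The concern holds. On the printed inputs and a two-sided test, power at 64 evaluable per arm is 80.1%, about 10 percentage points below the claim, and the shortfall against 90% is 22 evaluable patients per arm (86 − 64). The type II error for a 0.5 SD effect is about 20% rather than 10%.

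This rests on a two-sample comparison of means, equal arms, alpha 0.05 for each outcome and no gain from covariates. One-sided testing reduces the gap without closing it. Only an unstated baseline-outcome correlation of about 0.5 or more would close it. Because this is the sole justification of the sample size, it must be corrected.

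**What to change.** Keep 80 per arm and correct the Power section. Either of two wordings would do:

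1. State that 64 evaluable patients per arm give 80% power to detect 0.5 SD at two-sided alpha 0.05; the same number gives 90% power for about 0.58 SD.
2. If 90% for 0.5 SD is to stand, base the calculation on an ANCOVA adjusted for the baseline score, state and justify the assumed correlation (about 0.5 or higher), and name the baseline score as a covariate in the Statistical analyses section.

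State in either case that alpha is two-sided. The 20% drop-out step can stay as it is.

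The first option costs one sentence and no extra patients, though the stated power becomes less favourable. The second costs a justified assumption. If the sponsor instead wants 90% for 0.5 SD without relying on a correlation, the price is 108 enrolled per arm, or 2 × (108 − 80) = 56 more patients in total.

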### Intervention

The DiMaCoDeA-DM2 intervention will continue for a year and will consist of active screening, stepped care treatment and monitoring of depression/anxiety (see Figure 1).

**Figure 1 F1:**
[figure not shown]
**DiMaCoDeA Intervention**.

#### Screening

All patients with diabetes in the collaborating general practices will be screened for symptoms of depression and anxiety using the PHQ-9 and GAD-7.

#### Stepped care

A stepped care model has been used to design the intervention. This means that a basic treatment will be provided firstly, followed by intensified treatment when needed, i.e. in case of non-remission or worsening of symptoms. The DiMaCoDeA-DM2 stepped care treatment will comprise of the following three steps. The first step is psycho-education, which will consist of four 30-minute lessons provided by trained psychologists. At the end of the fourth lesson, the patient will fill out the PHQ-9 and GAD-7. If the patient scores below the cut-off score on both questionnaires (PHQ-9 < 7 and GAD-7 < 8), the treatment will be stopped and the patient will enter a phase in which symptom severity of depression/anxiety will be monitored. If the patient still suffers from significant depression/anxiety, as indicated by scores above the cut-off score, the patient will enter step 2. In the second step the course 'coping with depression and anxiety' will be offered to the patient. The course is based on the "coping with depression" course by Lewinson [29] and a "coping with anxiety" course [30]. The course consists of a self-help book and coaching. Coaching will be provided in the general practice office by trained psychologists and will take place once a week for half an hour. Depending on the most prominent complaints and on the patient's preference either the "coping with depression" course or the "coping with anxiety" course will be provided. A combination of the two courses is also possible. The course takes 10 weeks to complete. Halfway through the course and at the end of the course, the patient will fill out the PHQ-9 and GAD-7. If during the course the symptoms worsen, the patients will be offered the opportunity to start with step 3, even though step 2 has not been finished. In step 3, the GP will offer the patients medication for their symptoms of depression and/or anxiety. If medication is indicated, the general practitioner will have contact with the patient to discuss side effects and monitor the effect of the medication. Moreover, the course will be elongated with a maximum of 6 sessions in six months.

#### Monitoring

A crucial element of the intervention will be the frequent monitoring of depression and anxiety. During the DiMaCoDeA intervention, patients will fill out the PHQ-9 and GAD-7 every three months. If the patient has a score PHQ-9 ≥ 7 or GAD-7 ≥ 8, treatment will be offered; if step 1 has been completed, step 2 will be offered, and if step 2 has been completed, step 3 will be offered.

### Control group

The control group will receive care as usual. During the assessments (see below) the participants will fill out the PHQ-9 and GAD-7. If a patient in the control group has two consecutive PHQ-9 scores ≥ 15 or two consecutive GAD-7 scores ≥ 15, the general practitioner will be notified.

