### Assessments

All participants will fill out questionnaires at 7 time points: at baseline, 3, 6, 9, 12, 18 and 24 months. The primary outcomes are symptoms of depression and anxiety as measured by the PHQ-9 and GAD-7 [31,32]. The PHQ-9 is a screening tool that has nine items that correspond to the nine DSM-IV criteria of depression [31]. With the PHQ-9 the patients are asked how often in the last two weeks they were bothered by nine problems such as " Little interest or pleasure in doing things". Each item can be scored from 0 ("not at all") to 3 ("nearly every day"). The total score on the PHQ-9 ranges from 0 to 27. This score indicates the severity of the depressive symptoms; the higher the score, the more severe [31]. A study with primary care patients with diabetes found an optimal cut off score for depression screening of 7 [33]. The cut-off point of 7 on the PHQ-9, was the most optimal cut off score to predict major depressive disorder measured by a diagnostic interview [33]. Therefore the cut-off of PHQ-9 ≥ 7 will be used in this study. The GAD-7 will be used to assess anxiety symptoms. This questionnaire has been developed to assess generalized anxiety disorder, but can also be used as a screener for several anxiety disorders [32]. A cut-off score of 8 has been found to be the most optimal cut-off score, when used as a screener for several anxiety disorders [32]. Therefore, patients with a score GAD-7 ≥ 8 are considered as having significant anxiety symptoms.

During the baseline interview the Mini International Neuropsychiatric Interview (MINI) is administered to assess major depression and general anxiety disorder. The MINI will not be used as a selection criterion.

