## Discussion

This randomised controlled trial will test the effectiveness of a disease management model of anxiety and depression symptoms in Dutch patients with DM2 who are treated in primary care. We expect that the managed care intervention will contribute to enhanced treatment of depression/anxiety and a reduction of symptoms of anxiety and depression. We hypothesize that the intervention will also result in improved quality of life, reduced diabetes specific distress, better glycaemic control and lower health care cost. A first strength of the intervention is that it will largely take place in the general practice office. This will make it easier for patients to participate, because they do not have to travel to specialized mental health care institution. A second strength of the intervention is the stepped care approach. This means that the patient receives as much treatment as needed. Providing only the most intensive treatment to specific patients, will reduce the costs of the intervention. A third strength of the intervention is the monitoring of symptoms of anxiety and depression. It is known that anxiety and depressive symptoms often do recur, but are overlooked. It is therefore important to monitor patients to detect recurring anxiety and depressive symptoms and offer treatment if needed. A fourth strength is the RCT design. By randomising patients, possible confounders will be distributed randomly over the groups. Thereby, a possible different outcome between the two groups is most likely to be attributed to the intervention.

A possible limitation in the design is that the GP will be informed when a patient of the control group has two consecutive high scores. As a consequence the GP may start an intervention and this might interfere with care as usual. However, several studies have shown that focusing on detection, does not automatically lead to improved psychological care [22,23,37].

In conclusion, this trial will compare a disease management model with usual care. This model will improve detection of symptoms of depression and anxiety and will provide an easily accessible service to patients to improve their well-being. In the long-term this model might result in less diabetes complications and reduced mortality rate.

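### The GP-notification rule for control patients can never act on a first score of 15 or more at month 24, the last assessment

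*Protocol article*

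**What the plan says.** The Control group section of the protocol article says that controls complete the PHQ-9 and GAD-7 at the study assessments, and that when someone "in the control group has two consecutive PHQ-9 scores ≥ 15 or two consecutive GAD-7 scores ≥ 15, the general practitioner will be notified". The rule is limited to controls, and both high scores must be on the same scale.

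The Assessments section fixes when scores exist: "All participants will fill out questionnaires at 7 time points: at baseline, 3, 6, 9, 12, 18 and 24 months". Nothing is scheduled after month 24.

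The intervention arm has a lower, single-score trigger in the Monitoring section: "If the patient has a score PHQ-9 ≥ 7 or GAD-7 ≥ 8, treatment will be offered". It belongs to the programme period ("During the DiMaCoDeA intervention, patients will fill out the PHQ-9 and GAD-7 every three months"), and the Intervention section gives its length: "The DiMaCoDeA-DM2 intervention will continue for a year".

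The Discussion names GP notification of controls as a possible limitation, because the GP may then start treatment and so alter usual care. It does not discuss what happens at the last visit.

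**The concern.** A rule that needs two consecutive high scores works only while another assessment is still to come. At the final visit there is none. A control patient could record the maximum PHQ-9 total of 27 at month 24, and the rule as written would give the trial no reason to tell the GP.

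What is at stake is the patient's care after the trial, not the trial's estimate. The sponsor chose GP notification as its response to severe scores in controls, so the response should be able to work at every visit. The article itself gives grounds for not relying on routine contact to find such patients. On recognition, the Background says "Less than half of the depressed and/or anxious patients with diabetes are recognised as such", and on recurrence the Discussion says "It is known that anxiety and depressive symptoms often do recur, but are overlooked".

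**Working it through.** The plan gives no figure to reproduce here. The check sets the rule against the schedule.

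**Inputs**
- Trigger: two consecutive totals of 15 or more on the same scale, controls only (Control group).
- Assessments at months 0, 3, 6, 9, 12, 18 and 24 (Assessments).

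**Step 1. Earliest possible notification.** For a first high total at a given visit, the rule can fire at the next scheduled visit at the earliest, so the wait is the next visit minus the current visit.

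| First total of 15 or more at month | Next assessment | Earliest notification |
|---|---|---|
| 0 | 3 | 3 − 0 = 3 months later |
| 3 | 6 | 6 − 3 = 3 months later |
| 6 | 9 | 9 − 6 = 3 months later |
| 9 | 12 | 12 − 9 = 3 months later |
| 12 | 18 | 18 − 12 = 6 months later |
| 18 | 24 | 24 − 18 = 6 months later |
| 24 | none | never |

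At six of the seven assessments the rule delays notification. At one of the seven it rules it out. More exactly, at month 24 the rule fires only if the same scale was already at 15 or more at month 18.

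**Step 2. Does the stated reason for caution apply at month 24?** The reason is that a notified GP may treat the patient and so change usual care. Treatment started after the month-24 questionnaires are filled in cannot change those answers, and no later questionnaire follows. The reason does not apply.

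**Step 3. How many patients?** The article gives no rate of first high scores at month 24. If the anticipated 20% drop-out (Power section) is taken to apply by month 24, 80 × (1 − 0.20) = 64 controls remain. Suppose 2% to 10% of them first reach 15 at that visit; this range is an assumption with no basis in the article. That gives 64 × 0.02 = 1.3 to 64 × 0.10 = 6.4, or about 1 to 6 patients.

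**The case against.** The strongest reply is that the two-score rule is a deliberate trade-off. It separates persistent from passing symptoms and limits contamination of the control arm, which the Discussion acknowledges. Controls also stay under their GP and see the practice nurse every three months. In addition, the Discussion argues that detection does not automatically improve psychological care, so the gain from notification may be small.

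Much of this stands. It is a fair defence of the rule at visits before month 24, and it keeps the expected benefit modest. It does not defend month 24, where persistence cannot be checked by a later visit and contamination is no longer possible. A single score may be a fluctuation, but the GP can judge that only if told of it.

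A reader might infer more than the article supports:

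- **That the six-month wait after a first high score at month 12 or 18 is also a defect.** It follows from the disclosed trade-off, and shortening it would mean notifying controls before the final outcome.
- **That intervention patients have no safeguard at months 18 and 24.** The article states no score-triggered action at those visits, and although a late step 3 may continue after the first year ("the course will be elongated with a maximum of 6 sessions in six months"), no score rule is given for that period. But an article may leave post-programme care to the full protocol, so its silence is not an error.
- **That a positive PHQ-9 suicidality answer with a low total goes unanswered.** The eligibility criteria exclude suicidal ideation at entry, and a procedure for follow-up may well be in the full protocol.

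**Conclusion.** The point holds in a narrow form. Under the rule and schedule as published, a control patient whose first total of 15 or more occurs at month 24 cannot be notified to the GP. This is a gap in a rule that the article states in full, so it is not a matter of condensed detail. A fuller document could close it only by adding to the published rule or departing from it.

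The size is small: one of seven assessments, one arm, and probably a handful of patients, on an assumed rate that the article cannot confirm. It is a minor patient-safety improvement.

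A reader might also infer that different handling of high scores in the two arms biases the 24-month comparison. The article does not support that for this gap: whether or not the GP is told after the last questionnaire, the recorded scores are the same. Sample size, power and error rates are untouched.

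**What to change.** Add one sentence to the Control group section: at month 24, a single PHQ-9 or GAD-7 total of 15 or more is passed to the GP once that assessment is complete. Keep the two-score rule at all earlier visits.

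The same sentence can apply to the intervention arm, whose stated score trigger covers only the one-year programme. Doing so treats both arms alike at the end of the trial. If the full protocol already has an end-of-study procedure, a reference to it is enough.

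The cost is a short amendment, data already collected, and a few extra GP contacts after the final measurement. The questionnaire outcomes cannot change. The month-24 HbA1c is taken from patient charts, so the sponsor should use a value dated before any notification.
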